## Abstract

Background: Heart Failure (HF) is a common chronic disease that has a high readmission rate and is associated with worsening symptoms and major financial impacts. Disease management implemented during or after an HF hospitalization has been shown to reduce hospitalization and mortality rates. Particularly for outpatients, it is necessary to provide self-care interventions. Structured nurse-led support such as timely follow-ups, including phone calls, is beneficial for improving self-care assessments. Evidence for nurse-led support has been investigated but is less than conclusive. The aim of this study is to compare the effectiveness of a nurse-led structured intervention for outpatients with chronic HF against the usual medical care in terms of self-care behaviors and occurrence of symptom exacerbation or rehospitalization. Methods and analysis: This is a cluster-randomized controlled trial. A total of 40 facilities with certified HF nurses will be allocated to two-arm clusters at a 1:1 ratio, randomly to the intervention or usual care arms. A total of 210 participants will be assigned from the hospital. Participants will be adults aged 18 years or older diagnosed with chronic HF who are classified as Stage C according to the ACCF/AHA Heart Failure staging system. In the intervention group, patients will receive structured nursing support. This begins with weekly support, including phone calls, for the first month, then transitions to monthly support thereafter. The aim is to ensure the stability of their living conditions, promote medication adherence, and encourage self-management. In the control group, patients will receive the usual care. Primary outcomes will assess the improvement or continuation of self-care behavior as measured by changes in EHFScBS (European Heart Failure Self-Care Behavior Scale) scores. Secondary outcomes include occurrence of readmission within 30 days, 3 months, 6 months, and 1 year after discharge, duration of home care until readmission, and blood levels of BNP and NT-proBNP.

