### 2.2. Trial Design

We will conduct a cluster randomized controlled trial across different facilities to compare the efficacy of outpatient support by telephone and in person, as provided by a nurse.

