### 2.5. Randomization and Blinding

Eligible facilities will be gathered through open solicitation. The joint research institutions will be selected based on discussions among and comprehensive review by the internal meetings of this association. We will assign the intervention group (facility) and the control group (facility) at a 1:1 ratio through stratified randomization according to the volume of potential patients. Patients from each facility who provide their consent will be included as intervention subjects. Since the study involves a behavioral intervention without a potential placebo counterpart, it will be impossible to blind both investigators and participants to group allocations. However, data collection research assistants will be trained on consistent administration of measures and awareness of biases.

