### 2.7. Inclusion Criteria

Patients must have had one or more hospitalizations due to HF in the year preceding the index admission. Additionally, they must exhibit one or more of the following adherence-related issues:Living aloneDeterioration in familial support structuresMental health concerns, including depressionCognitive impairmentComplex medication regimens and instructionsExperiencing adverse drug reactions or side effectsInsufficient comprehension of medication regimenInadequate understanding of the disease process and prognosisChallenges in managing medication administration, weight monitoring, and fluid balanceMissing scheduled appointments (no-shows)

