## 8. Statistical Method

The Japan Nursing Association will submit the data received from the intervention and control groups’ medical institutions to a contracted data analysis organization for analysis. The between-group comparison of the change in self-care behavior continuity and changes in BNP and NT-proBNP in the baseline values at discharge and changes after intervention (1 and 3 months later) will be performed. The Spearman rank correlation coefficient will be used to measure the relationship between the scores of cardiac functions and the EHFScBS. The Mann–Whitney U-test will be used to compare the scores of the EHFScBS between the two groups with respect to patient backgrounds. The McNemar test will be used to analyze the changes in the two groups’ readmission and symptom deterioration rates, with the corresponding t-test employed for frequency, relative risk, and absolute risk reduction for risk difference. The presence or absence of readmission and the time to readmission between the intervention and control groups will be analyzed by the Kaplan–Meier method and tested for significance using the log-rank test. The Cox proportional hazard model and propensity score analysis will be used to compare between-group differences. Multiple imputation techniques will be employed to handle missing data, ensuring robustness and reducing bias in the findings. In the above analysis for the comparison, covariate adjustment from the baseline patient characteristics will be applied to gain efficiency in the estimation for the treatment effect, when it is necessary.

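### McNemar's test and a corresponding t-test are assigned to readmission and symptom deterioration in two independent, unmatched arms, where they cannot serve as the treatment comparison

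*Protocol article*

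**What the plan says.** Section 8 (Statistical Method) of the protocol article gives the rule in one sentence. It begins "The McNemar test will be used to analyze the changes in the two" groups, and goes on to name the rates and the second test: "readmission and symptom deterioration rates, with the corresponding t-test employed for frequency, relative risk, and absolute risk reduction for risk difference". The t-test is called corresponding; the word paired does not appear.

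The same section then compares presence of, and time to, readmission between the arms by Kaplan–Meier and log-rank, and lists a Cox model and propensity score analysis for between-group differences.

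The design is set out elsewhere:
- Section 2.2: "We will conduct a cluster randomized controlled trial across different facilities".
- Section 2.5: facilities are allocated "at a 1:1 ratio through stratified randomization according to the volume of potential patients".
- Abstract: "A total of 40 facilities with certified HF nurses will be allocated to two-arm clusters at a 1:1 ratio".
- Section 2.7: "Patients must have had one or more hospitalizations due to HF in the year preceding the index admission".
- Section 3.2 lists HF readmission at 30 days, 3 months, 6 months and 1 year after discharge.

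**The concern.** McNemar's test compares two binary observations on the same unit or on matched units. The sentence applies it to two groups that are neither. There are two ways to read it, and neither gives the treatment comparison.

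- **Between arms.** No pairs are defined. An analyst would have to invent them, and the result would depend on the invention.
- **Before against after within each arm.** The test can be computed, but it measures change over time, not the effect of allocation. Both arms can show a significant change when the intervention does nothing.

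The t-test half has a related fault. A t-test compares means; it does not estimate a relative risk or give one an interval.

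At stake are the clinical secondary results. The Discussion names fewer HF readmissions among the trial's purposes, and a contracted organisation will do the analysis and may follow the sentence as written.

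**Working it through.** The documents state no figure for these analyses, so there is none to reproduce. The event rates below are assumptions used to show how the test behaves.

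**1. Are there pairs between arms?** Section 2.2 gives a parallel cluster design. Section 2.5 gives 1:1 allocation stratified by patient volume. Strata are not matched pairs, and no matching of facilities or patients is described. There are no pairs.

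**2. What happens if pairs are imposed.** Assume 100 patients per arm with 18 and 31 events. Let k be the number of imposed pairs in which both members have the event. The discordant counts are b = 18 − k and c = 31 − k, so the McNemar statistic is

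(b − c)² / (b + c) = 13² / (49 − 2k) = 169 / (49 − 2k).

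The numerator is fixed by the data. The denominator depends only on how patients happen to be paired:

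| k | statistic | p |
|---|---|---|
| 0 | 169/49 = 3.45 | 0.063 |
| 2 | 169/45 = 3.76 | 0.053 |
| 3 | 169/43 = 3.93 | 0.047 |
| 6 | 169/37 = 4.57 | 0.033 |
| 13 | 169/23 = 7.35 | 0.007 |

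Over 5,000 random pairings p ran from 0.007 to 0.063, with a median of 0.033; 96% of pairings fell below 0.05. The ordinary two-sample chi-square on the same data gives the single value p = 0.033.

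**3. Type I error under random pairing.** Simulation used 20 clusters of 5 per arm and equal event rates of 20% or 30%.
- ICC 0: 0.049 to 0.051 with the asymptotic test, 0.034 to 0.037 with the exact test.
- ICC 0.05 (the value in Section 2.3): 0.071 to 0.075 asymptotic, 0.047 to 0.058 exact. The unadjusted chi-square gave 0.073 to 0.080.

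The between-arm fault is therefore an undetermined p-value, not gross inflation. The modest excess at ICC 0.05 comes from ignoring clustering, and the plain chi-square shares it.

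**4. Within-arm reading, readmission, one-year look-back.** Section 2.7 makes the before proportion 100%. Patients can only stay at yes or move to no, so all discordant pairs fall on one side. Assume 25% readmission in both arms, that is, no treatment effect:
- 105 per arm (Section 2.3): 105 × 0.75 = 78.75, about 79 discordant against 0. Exact p = 2 × 0.5^79 = 3.3e-24.
- After the 30% dropout in Section 2.3: 105 × 0.7 = 73.5, about 73. Then 73 × 0.75 = 54.75, about 55 against 0. Exact p = 2 × 0.5^55 = 5.6e-17.

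**5. Dependence on those assumptions.** With 105 per arm, independent before and after rates of 60% or 100% before and 20% or 30% after, and no treatment effect, the exact test rejected within an arm in 99% to 100% of simulations.

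**6. What else Section 8 provides.**

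| Outcome | Another between-arm method in Section 8? |
|---|---|
| Readmission, presence and time | Yes: log-rank, Cox |
| Readmission risk ratio and risk difference at the Section 3.2 horizons | None named |
| Symptom deterioration | None named |

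**The case against.** The best case for the plan is that McNemar is not the only analysis, and that it may be meant to describe change.

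- **Readmission has a suitable type of between-arm test.** This stands. A reader might infer that the readmission results as a whole are invalid. The documents do not support that, because log-rank and Cox follow in the same section.
- **Within-arm McNemar is a legitimate description.** This stands in part. Symptoms are recorded at baseline, and Section 6 repeats the baseline items at 3 months in controls, so paired within-patient data are planned at least there. A fall would be a real before–after change and misleads only if read as a treatment effect. But the sentence does not call the test descriptive, and Section 8 names no other test for symptom deterioration.
- **The extreme p-values depend on a chosen window.** This stands. A reader might infer that a fall is guaranteed in every analysis. The plan fixes no before period, and a 30-day or 3-month look-back that leaves out the index admission would not be 100%. Nor does eligibility fix any symptom at 100%.
- **The t-test is not called paired.** This stands: paired is the likely meaning beside McNemar, but it is an inference. The sentence can also be parsed as a t-test for frequency, with relative risk and absolute risk reduction as reported measures. On that parse the measures are right, but their between-arm method is still unstated and the only test attached to the rates is McNemar.
- **Readmission is not singled out for policy use.** This stands. The ethics section says the data will inform policy recommendations and names no endpoint, and the primary outcome is the EHFScBS.

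**Conclusion.** The sentence is wrong as written. As a treatment comparison, McNemar's test is undefined between these arms and is a non-randomised contrast within them.

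The consequence is limited to secondary outcomes. It is largest for symptom deterioration, which has no other named test, and for readmission risk ratios and differences at the fixed horizons. It is smaller for readmission overall because of the log-rank and Cox analyses.

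The lack of pairs follows from the design alone. The range 0.007 to 0.063 assumes 18/100 against 31/100. The values 3e-24 and 6e-17 assume a one-year look-back, 25% readmission in both arms, and 105 or about 73 evaluable patients per arm. They show that a significant within-arm fall says nothing about the intervention; they do not predict this trial's results.

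**What to change.** In Section 8, and in the analysis plan if it repeats the sentence:

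1. Delete McNemar's test and the corresponding t-test as treatment comparisons.
2. Compare the arms on readmission at each Section 3.2 horizon, and on symptom deterioration, with an independent-groups method that allows for facility clustering. A binomial or Poisson GEE or mixed model with facility as cluster would do, and agrees with the ICC of 0.05 in Section 2.3. The choice among these can be left to the analysis plan.
3. Report risk ratio and risk difference with 95% CIs.
4. If a within-arm McNemar result is kept, label it descriptive and define its before period.

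The cost is wording and some analysis work. Sample size, data collection and conduct do not change.

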## 6. Data Collection

Baseline information will be collected prior to intervention (Figure 2). This includes age, gender, duration since initial HF diagnosis, HF stage according to NYHA (New York Heart Association) classification, ACC/AHA classification, and MAGIC (Meta-Analysis Global Group in Chronic HF) score. Test values include height, weight (variation), BMI, blood pressure, LVEF (left ventricular ejection fraction), BNP and NT-proBNP blood tests, and scores on the “EHFScBS” for self-care behavior. Exercise tolerance is assessed using the ADL and Frailty Index and Clinical Frailty Scale, and cognitive function is evaluated using HDS-R and MMSE. Physical findings include symptoms of left HF (shortness of breath, dyspnea, rapid breathing, nocturnal cough, and orthopnea), symptoms of right HF (edema, right hypochondrial pain, loss of appetite, abdominal bloating, discomfort in the epigastric region), and symptoms caused by low cardiac output (fatigue, weakness, altered consciousness, restlessness, and decreased memory). Depression is assessed using the PHQ-9 and information on treatment status is collected. The presence or absence of remote monitoring system implementation, cardiac rehabilitation, past hospitalization episodes, utilization of HF notebook, family structure (living alone, decreased family functioning), discharge destination (home or facility with or without a nurse and primary care provider), social support system, and introduction of visiting nursing are also collected. Additionally, qualitative measures to capture patient experiences and satisfaction with the intervention will be reported, including details on support content (conducted in-person or by phone, with specific support details recorded) and patient reactions (content of patient statements) will be collected.

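### Propensity score analysis stands unranked beside the Cox model for the between-group comparison in a facility-randomised trial; it adds little and would be better kept as a labelled sensitivity analysis

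*Protocol article*

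**What the plan says.** Section 8 (Statistical Method) first plans Kaplan–Meier curves and a log-rank test for readmission and time to readmission. It then states: "The Cox proportional hazard model and propensity score analysis will be used to compare between-group differences". It gives no order between the two methods and no purpose for the score. It does not say whether the score would be used for matching, weighting, stratification or as a covariate. The section ends by planning adjustment for baseline patient characteristics, for efficiency, where judged necessary.

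On the design, Section 2.2 says "We will conduct a cluster randomized controlled trial across different facilities", and Section 2.5 allocates facilities "at a 1:1 ratio through stratified randomization according to the volume of potential patients". The Abstract gives the number: "A total of 40 facilities with certified HF nurses will be allocated to two-arm clusters at a 1:1 ratio". Patients are not randomised individually; Section 2.5 says "Patients from each facility who provide their consent will be included as intervention subjects", and that "it will be impossible to blind both investigators and participants to group allocations". Section 6 describes the baseline data, which run to well over 20 items.

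**The concern.** A propensity score estimates the chance of receiving treatment given patient characteristics. Here that chance is fixed by design, and assignment takes place at the facility. A patient-level score therefore models an assignment that was not made at patient level. Insofar as recruitment is comparable between arms, the fitted score describes chance imbalance. It can balance measured patient characteristics, but so can the covariate adjustment already planned. It cannot correct unmeasured differences between the 20 facilities in one arm and the 20 in the other.

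Two things are at stake. First, two analyses stand unranked for one contrast, so the choice of which to emphasise could be made after the results are known. Second, some uses of the score would cost patients or change what is being estimated, and the wording rules none of them out.

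**Working it through.** The documents give no figure for this point, so there is none to reproduce. The check has three parts.

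**1. Level of assignment.** Inputs: 40 facilities (Abstract), 1:1 allocation (Section 2.5), 210 patients (Section 2.3).

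- Facilities per arm: 40 / 2 = 20.
- Patients per facility: 210 / 40 = 5.25 on average.
- Allocation probability for a facility: 1/2 by design, so there is nothing to estimate.

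**2. Patients lost if the score were used for 1:1 matching.** This is a simulation with 40 facilities, 20 randomised to each arm, and 210 patients. Baseline covariates are normal and related to arm only by chance. The score comes from a logistic model. Matching is greedy nearest-neighbour, 1:1, without replacement, with 200 runs per setting. The assumptions not found in the documents are the caliper (0.2 or 0.1 SD of the logit), the number of covariates, and the intracluster correlation (ICC) of the covariates. Section 2.3 gives an ICC of 0.05 in the sample size calculation; that value is borrowed here as the base case for the covariates.

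Mean share of the 210 patients discarded:

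| Covariates in the score | ICC 0.05, caliper 0.2 (5th to 95th percentile) | ICC 0.05, caliper 0.1 | ICC 0, caliper 0.2 | ICC 0.2, caliper 0.2 |
|---|---|---|---|---|
| 5 | 19.5% (12.4 to 26.7) | 25.7% | 18.1% | 20.8% |
| 10 | 23.2% (15.2 to 31.4) | 28.4% | 21.6% | 26.4% |
| 15 | 26.4% (19.0 to 34.3) | 31.1% | 24.7% | 31.5% |
| 20 | 30.6% (22.8 to 39.0) | 34.4% | 27.9% | 35.8% |
| 30 | 35.9% (27.6 to 45.8) | 39.0% | 32.8% | 43.5% |

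In patients, the base case runs from 0.195 × 210 = 41 to 0.359 × 210 = 75. Across all settings tried, the mean loss was 18% to 46%; the top value comes from ICC 0.2, caliper 0.1 and 30 covariates. Weighting, stratification on the score, or entering the score as a covariate discards 0% by construction, unless trimming is added.

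**3. Difference in effect definition.** A covariate-adjusted Cox model estimates a conditional hazard ratio, whereas a weighted analysis estimates a marginal one. For illustration, exponential hazards were assumed, with one prognostic covariate of SD 0.5 or 1.0 on the log-hazard scale and 26% to 32% of patients having an event:

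| Conditional hazard ratio | Marginal, SD 0.5 | Marginal, SD 1.0 |
|---|---|---|
| 0.60 | 0.61 | 0.65 |
| 0.75 | 0.76 | 0.77 |

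The definitions can differ, but the gap is at most 0.65 − 0.60 = 0.05 in these cases.

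**The case against.** The strongest case for the plan is that randomising facilities does not guarantee comparable patients. Patients enter by consent, without blinding and apparently after their facility has been allocated, so recruitment could differ between arms. A propensity analysis is a legitimate way to probe that. This stands, and it is why the analysis need not be deleted. But Section 8 does not give this as the reason. Covariate adjustment handles the measured part of such imbalance, and neither method handles the unmeasured part.

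A second objection is that the form and covariates of the score belong in a full protocol or analysis plan that is not shown. That also stands, and their absence is not the point. The point is what the article does state: two methods, one purpose, no rank.

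A third is that patient-level regression cannot balance unmeasured facility differences either. That is true. Randomisation deals with those in expectation, and an allowance for facility in the model carries the remaining uncertainty.

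Three stronger readings are tempting, but the documents do not support them:

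- *A third of the patients will be lost.* This needs 1:1 caliper matching, which is never mentioned, and in the base case more than 20 covariates. Section 6 is a data-collection list, not a propensity model.
- *Power and the randomised comparison are lost, including for the primary self-care score.* The sentence follows the readmission analyses and is not tied to that score. The Kaplan–Meier, log-rank and Cox analyses remain, and nothing restricts them to matched patients.
- *A second, differently defined effect is certain.* The score could be used within the Cox model, and an unadjusted and a weighted Cox model both target a marginal hazard ratio.

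**Conclusion.** The concern holds as a minor improvement. Section 8 commits to a propensity score analysis beside the Cox model, unranked, for a contrast whose allocation is known by design and for which covariate adjustment is already planned. The firm consequence is two unranked results for one question.

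The rest is conditional. About 20% to 36% of the 210 patients would be dropped under 1:1 matching with a 0.2 SD caliper, a covariate ICC of 0.05 and 5 to 30 covariates; none would be dropped under other uses without trimming. The difference in effect definition is modest under the assumed hazards and event rates. Nothing here invalidates the trial.

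**What to change.** In Section 8, or in the analysis plan:

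- Name one Cox regression as the deciding between-group analysis of time to readmission. It should include all patients of the randomised facilities and adjust for a short list of Section 6 baseline items fixed in advance.
- Account for facility in that model by shared frailty or cluster-robust standard errors, which the current sentence does not mention. Choose one in advance, because a frailty hazard ratio is conditional on facility and the cluster-robust one is not.
- If a propensity score analysis is kept, label it a sensitivity analysis for differential recruitment. Use weights, without matching or trimming.

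The cost is a change of wording. It needs no new data and loses no patients.

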### 2.3. Sample Size

A sample size of 210 (105 in each arm) will allow us to detect a difference of four units in the EHFScBS scores with 80% statistical power. Assumptions are based upon data from the CHART-2 study, which estimated a mean clinical estimated difference of 4 in the EHFScBS before and after intervention, with a standard deviation of 8.5 [15,16]. The ICC was 0.05, and a dropout rate of 30% due to mortality or other reasons over one year was assumed, based on previous research results, in order to determine the sample size [17,18].

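### EHFScBS comparison names only a rank test and makes baseline adjustment conditional on an undefined need; a fixed baseline-adjusted model would fit the design better and is likely to gain power

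*Protocol article*

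**What the plan says.** All references are to the protocol article.

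- **Sizing (2.3).** "A sample size of 210 (105 in each arm) will allow us to detect a difference of four units", with 80% power. The inputs are an SD of 8.5, an ICC of 0.05 and 30% dropout.
- **Allocation (2.5).** Facilities are allocated 1:1 by "stratified randomization according to the volume of potential patients". The same section says: "Patients from each facility who provide their consent will be included as intervention subjects". It also says that neither investigators nor participants can be blinded.
- **Analysis (8).** The section opens with a between-group comparison of change from the discharge baseline to 1 and 3 months and attaches no test to it. It then says that the Mann–Whitney "U-test will be used to compare the scores of the EHFScBS between the two groups", and the sentence goes on to a qualifier about the patients' backgrounds that is hard to interpret. After the readmission analyses it says that the Cox model and "propensity score analysis will be used to compare between-group differences", without naming an outcome. It closes with the rule on adjustment: "covariate adjustment from the baseline patient characteristics will be applied to gain efficiency in the estimation for the treatment effect, when it is necessary".
- **Data (6).** Baseline EHFScBS is collected before the intervention.

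**The concern.** There are two weaknesses in what Section 8 states.

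**The named test does not match the design.** The trial is sized on a mean difference of 4 units with a clustering allowance, after stratified allocation of facilities. A Mann–Whitney test does not estimate a mean difference. In its standard form it takes no baseline score, no stratum and no facility effect.

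**The adjustment rule does not serve its own purpose.** The stated reason for adjusting is efficiency. That gain comes from the correlation between baseline and follow-up scores and exists whether or not the arms look balanced, so no observed data can make it necessary. With neither covariates nor a trigger fixed, the choice between adjusted and unadjusted results can be made after the data are seen.

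The choice matters more here than in an individually randomised trial. Section 2.5 implies, without saying so outright, that patients are recruited after their facility has been allocated, by staff who know the arm. Randomising facilities does not protect against differential selection of patients within them. A fixed adjustment for baseline EHFScBS would deal with imbalance on that score, though not with unmeasured differences. The present wording does not assure even that.

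**Working it through.** **Inputs.** Difference 4, SD 8.5, ICC 0.05, dropout 30%, 105 per arm (2.3); 40 facilities (Abstract). Assumed, because not stated: two-sided alpha 0.05, equal facility sizes, and a baseline-to-follow-up correlation r. It is unclear whether 8.5 is the SD of a score or of a change, so both are shown.

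**The plan's own figure.** Per arm, n = 2(1.96 + 0.8416)² × 8.5² / 4² = 70.9, so 71.
- Dropout only: 71/0.7 = 101.4, so 102 per arm and 204 in total (206 from the t-test's 72 per arm).
- With the ICC and 210 × 0.7/40 = 3.675 evaluable patients per facility: design effect 1 + 2.675 × 0.05 = 1.134. Then 71 × 1.134 gives 81, 81/0.7 gives 116, total 232.
- With the ICC and 210/40 = 5.25 enrolled per facility: design effect 1.2125, total 250.

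So 210 is close to the figure without clustering and is not reached when the stated ICC and 30% loss are both applied in the usual way.

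**Unadjusted power at 210.** Effective patients per arm: 105 × 0.7/1.134 = 64.8. The standardised effect is z = 4 / (8.5 × √(2/64.8)) = 2.68.
- Comparison of means: Φ(2.68 − 1.96) = 76.4%.
- Mann–Whitney, with relative efficiency 3/π = 0.955 under normality: z = 2.68 × √0.955 = 2.62, power 74.5%.

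Both figures allow for clustering through the design effect. They apply to follow-up scores if 8.5 is a score SD, and to change scores if it is a change SD.

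**Adjusted for baseline EHFScBS.** Residual variance is multiplied by 1 − r² if 8.5 is a score SD. If 8.5 is a change SD, the factor is (1 − r²)/(2(1 − r)) = (1 + r)/2. Power is Φ(2.68/√factor − 1.96), with the design effect left unchanged.

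| r | Power, 8.5 = score SD | Power, 8.5 = change SD |
|---|---|---|
| 0.3 | 80.2% | 91.4% |
| 0.4 | 83.2% | 89.3% |
| 0.5 | 87.2% | 87.2% |
| 0.6 | 91.8% | 85.0% |

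On the score-SD reading at r = 0.2 the factor is 0.96, z = 2.73 and power is about 78%, still short of 80%.

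**Equivalent total sample size for 80% power.** Unadjusted: 232. Adjusted on the score-SD reading: 71 × 0.91 × 1.134/0.7 gives 105 per arm (210) at r = 0.3, and 71 × 0.75 × 1.134/0.7 gives 87 per arm (174) at r = 0.5.

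**Where the gain comes from.** The rank test costs about 2 points (76.4% to 74.5%). Omitting the baseline score costs more: about 4 to 15 points against the unadjusted comparison of means for r from 0.3 to 0.6 on the score-SD reading, and 15 to 9 points on the change-SD reading.

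**The case against.** Several stronger readings are tempting, and the article does not support them.

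- **That Mann–Whitney is the primary test.** The sentence naming it carries the qualifier about patient backgrounds and may describe something else. The comparison of change is listed separately, and a condensed article may leave its test to the SAP. This stands. What remains is that no other test is named for EHFScBS between groups.
- **That baseline imbalance is left uncorrected.** A comparison of change uses the baseline score in part, propensity score analysis is planned, and adjustment is allowed. Correction is not assured, which is different from absent. That imbalance will occur is also not shown.
- **That propensity score analysis is optional.** Section 8 says it will be used; only covariate adjustment is conditional. Its outcome is not named, however, and it stands next to the readmission analyses, so it cannot be relied on for EHFScBS.
- **That adjustment always recovers the power lost to clustering.** On the score-SD reading this needs r of about 0.3 or more, and the document gives no r.
- **That power may be as low as 62%.** This is an unadjusted change-score comparison of means with r = 0.3 and 8.5 as a score SD: variance factor 2(1 − 0.3) = 1.4, z = 2.68/√1.4 = 2.26. Section 2.3 ties 8.5 to a before-and-after difference, which also fits a change SD, and then the figure is 76%.

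A mixed model is also not the only valid choice. The objection to the present wording does not depend on that choice: the article states a conditional rule, which goes beyond leaving detail to the SAP.

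**Conclusion.** The point holds in limited form. Section 8 makes baseline adjustment conditional on an undefined need, although its stated purpose requires no condition, and the only between-group test it names for EHFScBS neither estimates the quantity used for sizing nor, in standard form, takes baseline, stratum or facility.

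At 210 patients, unadjusted power is about 76% (74.5% for Mann–Whitney). Adjustment for baseline EHFScBS gives about 80 to 92% (score SD) or 91 to 85% (change SD) for r from 0.3 to 0.6. These figures rest on the assumed correlation, equal facility sizes, two-sided alpha 0.05, a normal approximation and a design effect unchanged by adjustment. Since allocation is stratified by patient volume, facility sizes may differ, which would tend to lower all the figures.

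This should be changed, but it does not show that the trial will be biased or that its primary result could not be interpreted.

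**What to change.** 1. In Section 8, delete the condition on covariate adjustment.
2. Pre-specify the primary analysis as the adjusted mean difference in 3-month EHFScBS from a linear mixed model. Include baseline EHFScBS and the facility-volume stratum as fixed covariates and facility as a random intercept, with a small-sample correction for 40 facilities. Apply it whatever the observed balance.
3. Keep Mann–Whitney and propensity score analyses as sensitivity analyses, and state the outcome to which each applies.
4. Reconcile Section 6 so that 3-month EHFScBS is clearly collected in both arms. The text gives a 3-month repeat of the baseline items for controls, but for the intervention arm describes repeat collection at readmission. Figure 1, whose image was not available for this review, is said to show questionnaire timing in both groups and may already settle this.

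Items 1 to 3 are wording in the protocol and SAP and use data already planned (baseline EHFScBS and the stratum). Item 4 is also wording if both arms already complete the scale at 3 months. If not, it adds one questionnaire per intervention patient.
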